## Abstract

**Introduction::**

Seborrheic alopecia (SA) has clinical manifestations, duration of disease, and priorities. In the current situation where there are many and complicated clinical treatments, Western medicine treatment can delay and control the development of the disease and promote hair regeneration. However, some patients may aggravate symptoms after taking the drug, and the condition is easy to repeat after stopping the drug. Acupuncture is an important method for non-surgical treatment of SA, and it has various methods, low side effects, high safety, and simple and economical. Therefore, we will use a clinical randomized controlled study to explore the effect of acupuncture on SA, and provide a new idea and reference for the treatment of this disease.

**Methods/design::**

We will select 60 patients diagnosed with SA. They will be randomly divided into intervention group and control groups. The control group will be given conventional treatment measures. The intervention group will receive acupuncture. Efficacy will be evaluated by comparing the skin lesion score and dermatological quality of life index before and after treatment.

**Discussion::**

This trial may provide evidence regarding the clinical effectiveness, safety, and cost-effectiveness of acupuncture for patients with SA.

**Trial registration number::**

CTR2000030430

## Introduction

1

Seborrhoeic alopecia (SA) is also called androgenic alopecia. SA is an androgen-dependent polygenic hereditary hair loss disease. The clinical manifestations of SA are mostly excessive secretion of scalp oil, greasy hair, large formation of dandruff, and sometimes itchy scalp.^[1]^ SA is more common in young men, and hair loss is often on the sides of the forehead and the top of the head. The number of women with SA is also increasing, but the symptoms are relatively mild.^[2]^ Because the disease affects aesthetics, it brings great mental stress and psychological burden to patients.^[3]^ The pathological characteristics of SA are mainly reflected in the following changes: changes in hair growth cycle, changes in subcutaneous blood flow, changes in sebaceous glands, and changes in hair follicle stem cells.^[4]^ The hair growth of SA patients showed changes in both the growth period and the stationary period. The proportion of hair growth in SA patients are shortened, the growth period increased, and the proportion of growth period and resting hair follicles decreased. The mechanism that causes these pathological changes is not completely clear. Recent studies have shown that the occurrence of SA is related to heredity, serum androgen levels, local androgen receptors, scalp subcutaneous blood flow, endocrine function, and psychosocial factors. About the treatment of this disease, oral medication is currently used.^[5]^ The most commonly used oral drug in clinical practice is finasteride. Clinical studies have shown that its effect in treating hair loss is clear, but the side effects of erectile dysfunction caused by reduced levels of sex hormones caused by long-term use are inevitable. In terms of topical use, minoxidil is mostly used clinically. Its mechanism may be to activate potassium channels, expand the subcutaneous blood vessels, and regenerate the hair and papilla blood vessels of the head.^[6]^ However, to obtain long-term effects as a topical drug, continuous medication is required.

SA has a relatively complete understanding in traditional Chinese medicine (TCM) theory. From ancient times to now, with the gradual improvement and development of TCM theory, the understanding of hair loss has become more detailed and a more complete diagnosis and treatment system has been formed. Since modern times, TCM has developed rapidly and has a deeper and deeper understanding of disease. Combined with the clinical symptoms of hair loss in modern medicine, hair loss is divided into seborrheic hair loss and alopecia areata. The former is defined as progressive loss of hair on the top of the head, which may be accompanied by strong oil secretion, itching, and increased dandruff; the latter is manifested as a sudden flaking of hair on the head, with no other accompanying symptoms.^[7]^ SA clinical manifestations, duration of disease, priorities vary. In the current situation of multiple and complicated clinical treatments, Western medicine oral medication can delay and control the development of the disease and promote hair regeneration.^[8]^ However, some patients may aggravate symptoms after taking the drug, and it is very easy to relapse after stopping the drug. As an important part of TCM, acupuncture has been widely used in the treatment of SA in recent years. By dialectical treatment, acupuncture points can be taken along with the evidence, which can play a role in replenishing Qi and regenerating essence, and nourishing liver and kidney. Acupuncture can improve local microcirculation, make the body full of Qi and blood, and then maintain hair. Acupuncture treatment of SA is not only a specimen that is effective, but also has small toxic and side effects, low price, and is easy to popularize. Therefore, we plan to use randomized controlled research methods to explore the clinical efficacy of acupuncture in the treatment of SA, and provide a way of thinking and reference for the treatment of SA.

## Methods/design

2

### Study design and settings

2.1

The study will be a randomized controlled trial divided into 2 parallel groups. This protocol is based on the Standard Protocol Project: Recommended Guidelines for Interventional Trials. If they agree, they will sign an informed consent form. Following the schedule described in Figure 1, only participants who read and agreed to the agreement and signed informed consent will be allowed to participate in the study. After patients will be included in this clinical observation, the research guidelines of randomized controlled trials will be strictly followed, and the randomized number table method are going to be used to divide the admitted patients into test groups and control groups on average.

**Figure 1 F1:**
[figure not shown]
SPIRIT figure for the schedule of enrollment, interventions, and assessments. DLQI = dermatology life questionnaire index, SPIRIT = standard protocol items: recommendations for interventional trials, TCM =traditional Chinese medicine.

### Participants

2.2

All cases in this study will come from acupuncture clinics and ward and dermatology clinics. This study intends to include a total of 60 samples. Eligible cases were randomly divided into treatment group and intervention group according to the digital randomization grouping method. (Fig. 2).

**Figure 2 F2:**
[figure not shown]
Study design flow chart.

#### Diagnostic criteria

2.2.1

The diagnostic criteria for Western medicine SA will refer to “*Clinical Dermatology”* (Edited by Zhao Yan, Jiangsu Science and Technology Press, December 2009, 1st edition). The proposed criteria are as follows:

(1)The clinical manifestations of men start from both sides of the forehead, and the hair gradually becomes thinner and thinner and extends toward the top of the head. The forehead hairline receded backward; the forehead was raised, forming an “M” -shaped high amount.(2)The clinical manifestations of women are that the hair on the top of the head is gradually thinner, the hairline on the forehead is retained, and hair remains on the pillow.(3)The skin lesion area is smooth as a mirror, and slender hairs are visible.(4)No obvious conscious symptoms or itching.

The diagnostic criteria for TCM SA will refer to the relevant content in the “Guiding Principles for Clinical Research of New Chinese Medicine”. The main symptoms: shiny hair, greasy dandruff, often a few hair sticks, hair thinning, and bald. Secondary symptom: accompanied by appetite, stool. Red tongue, yellow greasy fur, and pulsating veins.

#### Inclusion criteria

2.2.2

(1)18 to 50 years old (young and middle-aged), no gender restriction;(2)Western medical diagnostic standards that meet SA;(3)No other drugs that have an impact on the results of this study within 1 month before enrollment;(4)Sign the informed consent.

#### Exclusion criteria

2.2.3

Patients will be excluded if they meet the following criteria:

(1)Those who are younger than 18 years old or older than 50 years;(2)Other types of hair loss such as alopecia areata, congenital or traumatic hair loss, and chemotherapy or postpartum alopecia.(3)Patients with mental illness.(4)Those with local skin inflammation, erosion, or exudation.(5)Patients with previous hair transplantation.(6)Those with more serious underlying diseases.(7)Those who are pregnant or lactating.(8)Patients known to be allergic to the drugs contained in the test.

Note: Those who meet any of the above criteria are not allowed to join this study.

#### Case rejection or shedding criteria

2.2.4

(1)Participants found not to meet the inclusion criteria after inclusion;(2)In the course of treatment, patients who used the banned drugs specified in the plan themselves were used;(3)Those who cannot follow the doctor's orders due to reasons other than side effects, who have caused obstacles in determining the efficacy and safety assessment;(4)Those who were lost to follow-up during treatment and patients who requested to withdraw from the trial due to their own reasons.

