#### Suspension criteria

2.2.5

(1)In the treatment of this study, the patient was unexpectedly pregnant or had serious adverse reactions, and it was difficult to continue to receive acupuncture treatment.(2)During the implementation of this study, there was an obvious exacerbation or complications.

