### Randomization and blinding

2.5

According to the related literature and the actual situation, 60 cases were collected. Sixty cases will be referred to the random grouping method in “Chinese and Western Medicine Clinical Research Methodology” published by Science Press in 2008. The patients will be randomly divided into 30 cases in the treatment group and 30 cases in the control group. Grouping method: The computer generates random numbers, makes cards into envelopes, and draws them in the order of patient visits. Patients corresponding to the last digits are assigned to the treatment group, and patients corresponding to the last digits are assigned to the control group.

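### Section 2.2.4 sets post-randomisation rejection criteria without saying that these patients stay in the analysis; applied as exclusions, they undo the comparison by randomised group

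*Protocol article*

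**What the plan says.** Section 2.2.4 of the protocol article gives four criteria under the single heading "Case rejection or shedding criteria":

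1. "Participants found not to meet the inclusion criteria after inclusion".
2. During treatment, "patients who used the banned drugs specified in the plan themselves were used".
3. Patients unable to follow the doctor's "orders due to reasons other than side effects, who have caused obstacles in determining the efficacy and safety assessment".
4. "Those who were lost to follow-up during treatment and patients who requested to withdraw from the trial due to their own reasons".

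The first concerns eligibility. The other three are events during treatment, so they occur after randomisation.

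Section 2.2.5 is a separate list of suspension criteria. It covers unexpected pregnancy and serious adverse reactions that make further acupuncture difficult, and also this: "During the implementation of this study, there was an obvious exacerbation or complications". It contains no rejection wording.

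On allocation, section 2.5 says: "The patients will be randomly divided into 30 cases in the treatment group and 30 cases in the control group". Section 2.4.1 defines the efficacy index as the percentage reduction in symptom points from before to after treatment, and builds the total effective rate from it. Section 2.6 names tests for each type of data. Neither section says how patients who meet a criterion in 2.2.4 or 2.2.5 are counted.

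**The concern.** Criteria 2 to 4 depend on what happens to a patient after allocation, and those events can be related to outcome. Someone who sees no regrowth has a reason to leave or to try a banned drug. The efficacy index needs a post-treatment score, so a patient without one has no value unless a rule supplies it.

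Loss could plausibly differ between arms. The intervention arm receives needling on top of the control care. The control arm receives shampoo care with no sham procedure, so patients know what they are getting. Burden and disappointment need not be equal.

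If rejected cases are dropped from the analysis, the effective rate is calculated on a denominator that shrinks as failures leave, and mean scores are compared between groups that treatment experience has selected. Randomisation no longer protects the comparison, and the tests in section 2.6 no longer hold their nominal error rate.

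This goes beyond a detail that an article may leave to the analysis plan. The article states a rule in the language of rejection, and any later analysis plan that keeps these patients would have to override it.

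**Working it through.** **The plan's own figure.** The article gives no response rate, standard deviation, power or dropout allowance, so the 60 patients can be neither reproduced nor refuted. Only the size of the possible bias can be checked.

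**Inputs from the article.** 30 patients per arm (section 2.5); chi-square test for count data, two-sided, significance at P < .05 (section 2.6); total effective rate as a responder endpoint (section 2.4.1).

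**Inputs that are assumptions.** True effective rate 60% in both arms, so there is no real difference. Each failure is removed with probability q_A in the acupuncture arm and q_C in the control arm. No responder is removed.

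**Step 1: expected rate after removal.** An arm has 30 × 0.6 = 18 responders and 30 × 0.4 = 12 failures. The expected observed rate is about 18 / (30 − 12q).

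- q = 0: 18/30 = 60%.
- q = 0.25: 18/(30 − 3) = 18/27 = 66.7%.
- q = 0.5: 18/(30 − 6) = 18/24 = 75%.
- q = 0.3 against 0.2: 18/26.4 = 68.2% against 18/27.6 = 65.2%.

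The spurious advantage is 6.7 points at 25% v 0%, 15 points at 50% v 0%, and 3 points at 30% v 20%.

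**Step 2: chance of a false significant result favouring acupuncture.** Responders in each arm are Bin(30, 0.6), and removed failures are binomial given the number of failures. For a responders among n analysed on acupuncture, and b among m on control, z = (a/n − b/m) / √[P(1 − P)(1/n + 1/m)], with P = (a + b)/(n + m). This is the uncorrected chi-square test. Summing the exact probabilities of all outcomes with z > 1.96 gives:

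| Failures removed, acupuncture v control | False positive favouring acupuncture |
|---|---|
| 0% v 0% | 2.4% |
| 25% v 25% | 2.6% |
| 50% v 50% | 2.6% |
| 30% v 20% | 4.2% |
| 50% v 40% | 4.7% |
| 25% v 0% | 7.7% |
| 50% v 0% | 21.4% |
| 0% v 25% | 0.7% |

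The nominal value in one direction is 2.5%. The last row shows that the bias reverses when the control arm loses its failures.

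**Step 3: other response rates.** With removal from one arm only, true rates of 30%, 50% and 70% give a two-sided error of 6.7% to 7.3% when 20% of failures are removed, and 12.8% to 15.4% when 40% are removed. If all 60 are kept and the missing are counted as failures, it is 4.9% to 5.2%. That recovery is by construction, because only failures were removed in this model.

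**The case against.** The strongest objection is that the article never says that rejected patients' data leave the analysis. Section 2.2.4 is a list of criteria, section 2.6 names no analysis set, and the full protocol or analysis plan, which is not shown, may define one. This stands in part. A reader might infer that the trial will be analysed in completers only, but the text does not establish that. It does leave a rule whose natural reading is exclusion, with nothing to counter it.

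Several narrower objections also stand:

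- The heading joins rejection with shedding, and shedding may mean only dropout. Loss and withdrawal could then be a record of what happened and exclude nobody.
- Not every non-adherent patient is covered. The third criterion applies only where the cause is not side effects and assessment is obstructed.
- A reader might infer that patients with exacerbation are also rejected, so that treatment failures are hidden. Section 2.2.5 does not support this: suspension is a separate category. What is unstated is how those patients count.
- Unequal loss is plausible but not certain. Section 2.3.1 says that both groups are treated three times a week for three courses, and section 2.3.3 gives both the same education. With equal removal, the error rate stays close to nominal.

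The 21% figure is therefore the far end of an assumed range and should not be read as a forecast.

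**Conclusion.** The point holds in conditional form. Section 2.2.4 applies rejection language to post-randomisation events, does not separate stopping treatment from leaving the analysis, and is not offset by any statement that these patients remain in the comparison. If it is used as an analysis exclusion, the effective rate and scores are no longer compared by randomised group, and the result favours the arm that loses more of its failures.

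The size depends on how unequal the removal is. At an assumed 60% effective rate and 30 per arm, a modest imbalance (30% v 20% of failures) raises the false-positive chance favouring acupuncture from 2.4% to about 4%. One-sided removal of a quarter or a half of failures raises it to 7.7% or 21%. Equal removal of a quarter leaves it near 2.6%. Neither the response rate nor the removal probabilities come from the article.

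Section 2.8 says that recruitment has not started, so the wording can still be settled before any outcome is seen.

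**What to change.** - Reword section 2.2.4 so that meeting a criterion is recorded but does not remove a patient from the primary analysis.
- State that all 60 randomised patients, including those suspended under 2.2.5, are assessed where possible at the end of the 12 weeks (three courses of 4 weeks) and analysed in their allocated arm.
- Fix one missing-data rule in advance. One option is to count missing as ineffective for the effective rate, with multiple imputation as a sensitivity analysis. Counting missing as ineffective penalises the arm with more loss even when that loss is unrelated to outcome, so the sensitivity analysis matters. Other pre-specified rules would also serve.
- Use the 2.2.4 list only to define a per-protocol sensitivity analysis.
- Leave the treatment-stopping criteria in 2.2.5 unchanged.

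The cost is a change of wording, some extra follow-up contact with patients who stop treatment, and possibly a smaller estimated effect.

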#### Suspension criteria

2.2.5

(1)In the treatment of this study, the patient was unexpectedly pregnant or had serious adverse reactions, and it was difficult to continue to receive acupuncture treatment.(2)During the implementation of this study, there was an obvious exacerbation or complications.

### Interventions

2.3

#### Control group

2.3.1

Patients in the control group will receive regular shampoo care. The specific content is: keep washing your hair with warm water once every 2 days to reduce seborrhea and scalp itching to reduce scalp and hair damage caused by scalp pain and itching. Shampooing should not be too frequent. Frequent shampooing will promote the secretion of sebaceous glands and increase seborrhea. The intervention group and the control group were treated 3 times a week, 4 weeks as a course of treatment, and a total of 3 courses of treatment.

#### Intervention group

2.3.2

The intervention group will be treated with acupuncture on the basis of the control group. We will select *Baihui*, *Fengchi*, *Sishencong, Zusanli, Neiting*, and *Taichong* as the main points. Secondary acupuncture points: those with hair loss on both sides of the crotch, plus *Touwei*; those with scalp pruritus, enlarged *Dazhui*; those with more oil secretion, plus *Shangxing*. Specific operation method: the patient takes the prone position, the forehead rests on the square pillow; conventional disinfection, after positioning the needle, hold the acupuncture needle on the left and place it on the acupoint; use the index finger to quickly tap the exposed needle handle to make the needle tip stab under the skin; then remove the needle tube and pierce the needle into the acupoint. Insert the needle perpendicular to the skin surface with a 1.5 inch needle. After leaving it for 30 minutes, the needle was started. The positioning and operation of common acupuncture points are performed according to the positioning and operation of acupuncture points in the second edition of the Chinese “Twelfth Five-Year Plan” textbook “Meridian Acupoints” (China Traditional Chinese Medicine Press, chief editor Shen Xueyong). Needle selection: Sterile acupuncture needles (0.25 × 25 mm, 0.30 × 40 mm) produced by Suzhou Acupuncture Supplies Co. Ltd.

#### Basic treatment

2.3.3

For the sake of patient's health, this study will provide basic treatment-rehabilitation education for 2 groups of patients.

(1)SA patients should pay attention to the combination of work and rest, especially mental workers should pay attention to avoid long-term tension and excessive brain use. Consistent exercise is the key to strengthening your body and protecting your hair. Regular exercise is also one of the ways to eliminate tension, and tension is also an important cause of hair disorders.(2)Diet adjustment needs to pay attention to the balance of nutritional intake, the richness of food types, and the reasonable intake of various foods to ensure the necessary nutrients for hair growth. In particular, it is necessary to ensure the intake of nutrients that are beneficial to hair growth, such as soybeans, walnuts, black sesame, and cereals that are rich in vitamins and trace elements; reduce fat intake, especially animal fats and sugars, and spicy Food intake does not aggravate sebum spillage and affect hair growth.(3)During the treatment, we will briefly explain the cause of SA to patients, and inform the prognosis of the disease and daily precautions.

### Outcome measures

2.4

#### Primary outcome measures

2.4.1

Primary outcome measures will be assessed using symptom scores. The clinical efficacy will be determined by referring to the “Guiding Principles for Clinical Research of New Chinese Medicines” and “Clinical Dermatology”. Establish a standard for determining the efficacy (refer to the 4-point scoring method for clinical research guidelines for new Chinese medicines) to determine the efficacy index using the nimodipine method. That is [(pre-treatment points-post-treatment points) ÷ pre-treatment points] × 100%. Clinical total effective rate = clinical cure rate + clinical apparent efficiency + clinical effective rate. In addition, we will refer to the relevant standards in “Clinical Dermatology” and develop clinical efficacy observation scores based on clinical practice. Hair loss (comb test), scalp condition (greasy scalp, itching, dandruff, folliculitis), hair regeneration (new hair density, new hair texture) total 7 indicators, divided into 4 levels for evaluation.

#### Secondary outcome measures

2.4.2

Secondary outcome measures will be assessed based on the psychological status of SA patients. We will use the Dermatology Life Questionnaire Index and hair growth self-evaluation questionnaire to evaluate specific indicators.

### Randomization and blinding

2.5

According to the related literature and the actual situation, 60 cases were collected. Sixty cases will be referred to the random grouping method in “Chinese and Western Medicine Clinical Research Methodology” published by Science Press in 2008. The patients will be randomly divided into 30 cases in the treatment group and 30 cases in the control group. Grouping method: The computer generates random numbers, makes cards into envelopes, and draws them in the order of patient visits. Patients corresponding to the last digits are assigned to the treatment group, and patients corresponding to the last digits are assigned to the control group.

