### Statistical analysis

2.6

SPSS for windows 24.0 statistical analysis software will be used for calculation, and normality test and homogeneity test of variance will be performed on each group of data. For measurement data in which the data conforms to the normal distribution, we will use the mean ± standard deviation. For non-normally distributed measurement data, the median ± quartile interval is used. General data comparison between the 2 groups using independent sample *t* test. Comparisons before and after treatment will be performed using *t* test for paired data. One-way analysis of variance will be used for comparison between groups. X^2^ test will be used for count data, and nonparametric rank sum test will be used for rank data. All statistical tests are two-sided. *P* < .05 indicates a significant difference.

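### The named one-way ANOVA uses neither baseline score nor sex, and allocation is unstratified: precision is lost, but the test stays valid

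*Protocol article*

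**What the plan says.** - **Prognosis by sex.** Section 1 states: "The number of women with SA is also increasing, but the symptoms are relatively mild". Section 2.2.1 describes the sexes separately; for women, "The clinical manifestations of women are that the hair on the top of the head is gradually thinner", with the frontal hairline kept.
- **Eligibility.** Section 2.2.2: "18 to 50 years old (young and middle-aged), no gender restriction". No expected share of women is given.
- **Allocation.** Section 2.5: "The patients will be randomly divided into 30 cases in the treatment group and 30 cases in the control group". The mechanism is "The computer generates random numbers, makes cards into envelopes, and draws them in the order of patient visits". No stratification factor is named.
- **Primary outcome.** Section 2.4.1 defines an efficacy index as the fall in symptom score divided by the pre-treatment score, times 100%, and sums response categories into a total effective rate. The score has seven four-level items: comb test, greasiness, itching, dandruff, folliculitis, new hair density and new hair texture.
- **Analysis.** Section 2.6 names one-way analysis of variance for comparisons between groups, chi-square for counts and a rank sum test for ranked data. No covariate is named, and the text does not say whether the ANOVA takes the post-treatment score or the index.

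**The concern.** By the article's own account, sex is related to severity. Baseline severity also enters the primary index as its denominator: for the same absolute fall, a milder patient shows a larger percentage. Yet neither sex nor baseline score is used in the allocation or in the named between-group test.

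Two things are at stake. First, variation that a recorded baseline score could explain stays in the error term, in a trial with only 30 per arm. Second, if the arms happen to differ in their share of women, the unadjusted estimate in that trial may move for a reason unrelated to acupuncture, and the named analysis cannot separate the two.

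**Working it through.** **No stated figure to reproduce.** Section 2.5 gives 60 patients without an effect size, standard deviation or power. For orientation, 30 per arm at two-sided 0.05 has 49% power for a standardised difference of 0.5, and needs about 0.72 for 80%.

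**1. Chance of a sex imbalance.** With W women among 60 and 30 drawn to treatment, the number of treated women X is hypergeometric(60, W, 30). The arms differ by |2X − W| women, and 6 of 30 is 20 percentage points.

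| Women (assumed) | P(gap ≥ 20 points) |
|---|---|
| 12 (20%) | 0.104 |
| 18 (30%) | 0.158 |
| 24 (40%) | 0.187 |
| 30 (50%) | 0.196 |

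An odd W cannot give a gap of exactly 6. With 15 women, a gap of 5 or more has probability 0.233 and of 7 or more 0.072.

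**2. Effect on the percent index.** Assumptions not in the article: score 0–21; baseline means 12 (men) and 9 (women), or 13 and 7; within-sex SD 3; noise SD 2; 8,000 simulated trials per scenario.

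- No treatment effect, all trials: unadjusted rejection 0.048–0.053 and mean estimate about 0.
- Trials with at least 20 points more women on treatment, everyone improving 3 points: the estimate shifts by about 2 to 3 index points (12 v 9) or 4.7 to 4.8 (13 v 7), against an SD of the estimate of about 6 to 7.
- Same imbalance, everyone improving 25%: shift about 0.
- Imbalance of at least 20 points in either direction, 13 v 7, equal absolute improvement: false rejection about 0.09 unadjusted, 0.04–0.05 with sex in the model.

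**3. Precision, by hand.** Take 30% women, baselines 12 v 9, equal absolute improvement, extra benefit 1.2 points. Standard error = SD × √(2/30) on the post-treatment score.

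- No covariate: variance 3² + 0.3 × 0.7 × (12 − 9)² + 2² = 14.89; SD 3.86; SE 1.00.
- Sex: variance 9 + 4 = 13; SD 3.61; SE 0.93.
- Baseline score: variance 4; SD 2; SE 0.52.

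**4. Power, by simulation.** Same set-up, 18 women. Extra benefit is 1.2 points (equal absolute) or 15 percentage points on top of 25% (proportional). Monte Carlo error is about 0.005.

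| Scenario | Index, no covariate | Index + sex | Post score, no covariate | + sex | + baseline | + baseline + sex |
|---|---|---|---|---|---|---|
| 12 v 9, absolute | 0.458 | 0.473 | 0.226 | 0.249 | 0.604 | 0.598 |
| 13 v 7, absolute | 0.392 | 0.452 | 0.174 | 0.243 | 0.600 | 0.587 |
| 12 v 9, proportional | 0.748 | 0.742 | 0.559 | 0.594 | 0.872 | 0.865 |
| 13 v 7, proportional | 0.678 | 0.676 | 0.475 | 0.613 | 0.882 | 0.878 |

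With no treatment effect, all of these analyses rejected in about 5% of trials.

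**The case against.** The strongest reply is that nothing here is wrong. Randomisation makes the estimate unbiased, and the unadjusted test already allows for chance imbalance in every covariate, sex included. That stands, and the simulated error rates confirm it.

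A reader might infer that unstratified allocation is a bias able to create or hide an effect. The article does not support this.

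- The shift on the index requires improvement that is not proportional to baseline, and the article says nothing on that. If improvement is proportional, dividing by baseline removes the severity difference.
- Even an extreme constructed case fails to give a false positive. Let women start at 6 and men at 12, let everyone improve by 3, and set a 30% cut-off. Women score 50% and men 25%, so 10 women against 5 gives 10/30 v 5/30 effective. Chi-square = 60 × (10 × 25 − 20 × 5)² / (30 × 30 × 15 × 45) = 2.22, p = 0.136.
- The different hair-loss pattern in women does not enter the primary score directly: none of the seven items grades hairline against crown. Only the remark about milder symptoms carries the argument, and it is general background without figures for the enrolled women.

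It is also fair that sex is only a proxy for baseline severity. In the table, once baseline score is in the model, sex adds nothing, because in these scenarios sex acts only through baseline. Sex helps further only if it predicts outcome beyond baseline.

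Finally, a condensed article may leave strata and covariates to a fuller document. Silence on them is therefore no fault. What remains is that the article does name a between-group method, and one-way ANOVA has room for one factor only.

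**Conclusion.** The point holds as one about precision and interpretation. The named analysis is valid but inefficient.

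In the assumed scenarios, sex alone raises power on the post-treatment score by about 2 to 14 points. Baseline score raises it far more, for example from about 0.23 to 0.60. If the ANOVA is meant for the percent index, which already uses baseline as a divisor, the fairer comparison is 0.46 against 0.60, or 0.75 against 0.87 under proportional improvement (12 v 9). On the index itself, adding sex gains about 1 to 1.5 points with baselines 12 v 9 and about 6 with 13 v 7 if improvement is equal in absolute terms, and nothing if it is proportional.

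The exposure to sex imbalance is real but modest: about a 10% to 20% chance of a 20-point gap, and a shift smaller than the standard deviation of the estimate. All sizes rest on the assumed share of women, baseline means and variances, none of which the article gives. This is an optional improvement.

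**What to change.** - **Section 2.6 (main change).** For the primary symptom score, replace the one-way ANOVA by an ANCOVA: post-treatment score on group, baseline score and sex. Report the adjusted group difference with its 95% confidence interval. Keep the percent index and effective rate as supporting summaries; the chi-square and rank sum tests named for counts and ranks take no covariate, so this change does not adjust them.
- **Section 2.5 (optional).** Prepare separate envelope sequences for men and women, each in blocks of varying size. If this is done, sex belongs in the model as a design factor.

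**Cost.** One or two model terms, using data already collected. In the scenarios above, sex on top of baseline costs at most about one point of power. With two sequences, arm totals may miss exactly 30/30 by about half a block per stratum. Section 2.8 says recruitment has not started, so both changes can still be made in advance.
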